# ALT GIST

## **9.2. Progression free survival (disease progression or death)**

The length of time from either (i) randomization (if patients have not yet commenced treatment) or (ii) commencement of therapy (if patients are randomized during the first cycle of imatinib) until disease progression. Disease progression is defined according to RECIST 1.1

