## 3. AIM AND OBJECTIVES

|                                     |                                                                                                                                                                                                                                                                                                                                                                                                                                                              |
|-------------------------------------|--------------------------------------------------------------------------------------------------------------------------------------------------------------------------------------------------------------------------------------------------------------------------------------------------------------------------------------------------------------------------------------------------------------------------------------------------------------|
| General aim                         | To determine if an alternating regimen of imatinib and regorafenib has sufficient activity and safety to warrant further evaluation as a first line treatment for metastatic GIST.                                                                                                                                                                                                                                                                           |
| Primary objective (endpoint)        | 

▪ Objective tumour response by 9 months as determined by RECIST v1.1. from either the date of (i) randomization (if patients have not yet commenced treatment) or (ii) commencement of therapy (if patients are randomized during the first cycle of imatinib)

                                                                                                                                               |
| Secondary objectives (endpoints)    | 

▪ PFS as calculated from either the date of (i) randomization (if patients have not yet commenced treatment) or (ii) commencement of therapy (if patients are randomized during the first cycle of imatinib)

▪ Clinical benefit rate (SD + PR + CR) following 3 cycles (24 weeks) of treatment

▪ Time to treatment failure

▪ Safety/toxicity/tolerability

▪ Overall survival

 |

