# ALT GIST

h: Liver function testing must also be performed weekly in the alternating treatment arm during regorafenib use for the first 2 cycles. AST, ALT and bilirubin must be monitored weekly during regorafenib use for the first 2 cycles of the patient taking regorafenib. Site or local laboratory may be used.

i: blood collected for drug (imatinib) level testing. Refer to Biological Sampling Handbook for details of collection and processing. Documentation of compliance with treatment during the preceding cycle should be documented in the eCRF

j: blood collected for drug (regorafenib) level testing. Refer to Biological Sampling Handbook for details of collection and processing. Documentation of compliance with treatment during the preceding cycle should be documented in the eCRF

k: blood for **optional** translational research will be collected at these timepoints. Refer to Biological Sampling Handbook for details of collection, processing and storage

l: for the first 12months, CT scans are performed 8 weekly from randomisation after which CT scans are performed 12 weekly. Imaging of the brain should be undertaken if clinically indicated. CT scans should continue as per the protocol until PD

m: weekly blood pressure measurements are required from the commencement of regorafenib in cycle 1 until the completion of cycle 2.

n – only in those Arm B patients enrolled in the PET substudy. Patients randomised to have two scans and timing is based on a second randomisation - either PET scans during imatinib washout period, or regorafenib washout period. Depending on allocated arm, PET scans to be performed at the completion of regorafenib or imatinib tablets (or up to 2 days prior) and before the commencement of the subsequent imatinib or regorafenib cycle (or up to 2 days prior). These scans are to be performed in Cycle 2 at the earliest or in a subsequent cycle (at the first opportunity after a complete cycle of treatment with no dose modifications is given).

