## **9.3. Clinical benefit rate at 3 cycles (24 weeks)**

The clinical benefit rate will be calculated by summing the number of participants assessed as having a complete response, partial response or stable disease within the first 24 weeks from randomisation, and dividing this by the total number of participants evaluable for response (according to RECIST Version 1.1) within the first 24 weeks.

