## **9.4. Time to treatment failure**

Time to treatment failure is defined as the time from either (i) randomization (if patients have not yet commenced treatment) or (ii) commencement of therapy (if patients are randomized during the first cycle of imatinib) to treatment discontinuation for any reason, including disease progression, treatment toxicity, patient preference, or death.

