## **9.6. Overall survival**

Overall survival is defined as the interval from either (i) randomization (if patients have not yet commenced treatment) or (ii) commencement of therapy (if patients are randomized during the first cycle of imatinib) to date of death from any cause, or the date of last known follow-up alive.

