## 13.2. Statistical Analysis

Analyses will include all patients who were randomised. Treatment activity will be assessed by the proportion, together with the 95% confidence interval, of patients having an objective response at or before 9 months. Similar proportions will be determined in the control group,

Time-to event endpoints of progression free and overall survival and time to treatment failure will be described using the method of Kaplan-Meier. Treatment failure is defined as the first event before 12 months of death, disease progression and unacceptable toxicity causing study treatment to cease or patient preference to cease therapy. For purposes of treatment failure, only events in the first 12 months will be considered. Patients not experiencing a treatment failure within 12 months will be censored at 12 months. While there will not be any formal comparisons between the two groups, exploratory comparative analyses may be performed. For time-to-event outcomes, these will include univariate logrank and multivariate proportional hazards comparisons. Other exploratory analyses will also be performed as appropriate.

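### For patients already on imatinib, the PFS, OS and treatment-failure clocks start before randomisation and count up to 25 event-free days as time at risk: a small upward bias in each arm's curve

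*Protocol*

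**What the plan says.** For patients already on imatinib at randomisation, three time-to-event endpoints start at the first imatinib dose, worded each time as "commencement of therapy (if patients are randomized during the first cycle of imatinib"):

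- PFS (section 9.2): "commencement of therapy (if patients are randomized during the first cycle of imatinib) until disease progression".
- Time to treatment failure (section 9.4): "commencement of therapy (if patients are randomized during the first cycle of imatinib) to treatment discontinuation for any reason".
- OS (section 9.6): "commencement of therapy (if patients are randomized during the first cycle of imatinib) to date of death from any cause".

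All other patients start at randomisation. The primary response window (synopsis, sections 3 and 9.1) uses the same two-part origin.

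Inclusion criterion 3 caps the prior imatinib at 25 uninterrupted days. The note to the study schema allows randomisation on any of those days and counts them into cycle 1.

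Other clocks run from randomisation for everyone. Section 8.1 says "CT scans are performed 8 weekly from randomisation" during the first 12 months. Section 9.3 counts clinical benefit "within the first 24 weeks from randomisation", whereas section 3 and the synopsis word that endpoint as "following 3 cycles (24 weeks) of treatment".

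Section 13.2 plans Kaplan-Meier description and no formal comparison between arms. It limits treatment failure to 12 months: "Patients not experiencing a treatment failure within 12 months will be censored at 12 months".

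**The concern.** A patient who died or stopped imatinib between the first dose and the intended randomisation never enters the trial. For those who do enter, the days between are guaranteed free of death and of treatment discontinuation. Progression is judged against measurements recorded on study, on scans timed from randomisation, so study-assessed progression cannot fall there either. Counting those days as time at risk is immortal time.

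Stratification by prior imatinib spreads the lead-in evenly over the arms but does not remove it from either curve. In a non-comparative design the curves of the single arms are the result that is reported. Each curve also mixes patients with and without a lead-in, and the scans fall at different points on the two clocks.

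**Working it through.** No sample size, event count or threshold in the protocol rests on PFS, OS or treatment failure, so there is no stated figure to reproduce. The checks below size the effect.

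**Inputs.** Maximum lead-in L = 25 days (inclusion criterion 3). Median PFS on imatinib about 24 months = 730.5 days (section 1). Failure horizon 12 months = 365.25 days (section 13.2), taken to run from the origin in section 9.4. Arms of 38 and 22 (section 13.1). Assumptions: exponential times measured from randomisation, and a pre-treated share f, which the protocol does not give and which is varied here.

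**1. Size of the lead-in.** 25/730.5 = 3.4% of the median; 25/365.25 = 6.8% of the failure window.

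**2. Median PFS.** With λ = ln 2/730.5, the curve on the protocol's clock is S(t) = (1−f)·exp(−λt) + f·exp(−λ(t−L)) for t > L. Setting S(t) = 0.5 gives a median of 730.5 + ln[(1−f) + f·exp(λL)]/λ.

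| f | L (days) | Shift in median |
|---|---|---|
| 0.25 | 12.5 | +3.1 days (0.4%) |
| 0.5 | 12.5 | +6.3 days (0.9%) |
| 0.5 | 25 | +12.6 days (1.7%) |
| 1 | 25 | +25.0 days (3.4%) |

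**3. Twelve-month PFS.** For a patient with the full lead-in: exp(−λ·340.25) = 72.4%, against exp(−λ·365.25) = 70.7%.

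**4. Twelve-month treatment failure.** Real risk time is 365.25 − L, that is, between about 340 days (11.2 months, full lead-in) and 365 days (none). With true failure F, the reading at the full lead-in is 1 − (1−F)^(340.25/365.25): 30% → 28.3%, 40% → 37.9%, 50% → 47.6%. These figures apply if every patient has all 25 days. Any smaller share or shorter lead-in gives less.

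**5. Between arms.** Let q be an arm's pre-treated share and T = 730.5 days of follow-up. The crude event rate on the protocol's clock is [(1−q)(1−e^(−λT)) + q(1−e^(−λ(T−25)))] / [(1−q)(1−e^(−λT))/λ + q(25 + (1−e^(−λ(T−25)))/λ)]. With no true effect, the rate ratio is 1.00 for equal shares, 0.99 for 40% against 60%, and 0.95 for 0% against 100%.

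**6. Scans.** On the PFS clock the scans fall at days 56, 112, 168 and 224 for untreated patients, and as late as days 81, 137, 193 and 249 for pre-treated ones.

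**7. Primary window.** Nine months is 273.9 days. The scans of weeks 8 to 32 fall inside it on either origin (the last at day 224, or up to day 249). Week 40 falls outside on either (day 280, or up to day 305). No scheduled scan is gained or lost.

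**8. Clinical benefit rate.** Section 9.3 ends at day 168 after randomisation, which is the week-24 scan. Three cycles of treatment, with 25 prior days counted in, end at day 168 − 25 = 143, between the scans of days 112 and 168.

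**The case against.** The strongest reply is that the origin is deliberate. It is worded alike for response, PFS, treatment failure and OS, and it matches the rule that prior imatinib counts into cycle 1. Inclusion criterion 12 lets an untreated patient start up to 14 days after randomisation. Under the present rule, time zero therefore lies 0 to 14 days before the first dose for everyone. Under a plain randomisation origin it ranges from 14 days before to 25 days after. This stands as a reason to allow the present origin, but it does not make the selected days time at risk. Delayed entry keeps the origin and removes the bias.

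The second reply is size. At 40%, the 95% half-width, 1.96·√(0.4·0.6/n), is about 16 points for n = 38 and 20 points for n = 22, against a shift of at most 2.1 points. That stands and keeps the point minor.

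Third, delayed entry might be in a statistical analysis plan that is not at hand. If so, only a cross-reference is needed. The origin itself is fixed in the protocol.

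A reader might infer four stronger things that the document does not support:

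- *Pre-treated patients are shown to be unprogressed at randomisation.* No criterion asks for this; criterion 4 on progression concerns adjuvant therapy only. The event-free interval for PFS follows from how and when progression is assessed.
- *Pre-treated patients have at most 11.2 months of risk in the failure window.* That is the minimum, reached only at the full 25 days.
- *Treatment failure loses a known amount of early imatinib intolerance.* The protocol gives no such rate.
- *The primary endpoint is distorted.* No scheduled scan moves across its boundary.

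**Conclusion.** The point holds as a minor one. PFS, OS and treatment failure carry up to 25 days of guaranteed event-free time in pre-treated patients. Each arm's estimates move in the favourable direction, by at most 25 days on a 24-month median and by about 6 to 13 days if half the patients are pre-treated. A 40% failure rate at 12 months would read no lower than 37.9%. These figures rest on a constant hazard and on an assumed pre-treated share.

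A material bias between arms should not be inferred: prior imatinib is a stratification factor, and comparisons are exploratory only.

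The two wordings of the clinical benefit rate differ by up to 25 days for pre-treated patients. Section 9.3 already uses randomisation and agrees with the scan schedule, so this is a matter of reconciling text.

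**What to change.** 1. In sections 9.2, 9.4 and 9.6, either use randomisation as time zero for all patients, or keep the start of therapy and enter pre-treated patients into the risk set at randomisation (delayed entry). Report the other as a sensitivity analysis. With delayed entry the first 25 days of the curve rest mainly on untreated patients, so numbers at risk should be shown, above all in the arm of 22.
2. State whether the primary response window (synopsis, sections 3 and 9.1) keeps its start-of-therapy origin, so that any difference from PFS is explicit.
3. Bring the wording of the clinical benefit rate in the synopsis and section 3 into line with section 9.3.
4. Report, by arm, the number of pre-treated patients and their days of prior imatinib.

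The cost is wording and analysis code, with no new visits, data or patients. The downside is that times shorten by at most 25 days in pre-treated patients if randomisation becomes time zero.

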## **9.3. Clinical benefit rate at 3 cycles (24 weeks)**

The clinical benefit rate will be calculated by summing the number of participants assessed as having a complete response, partial response or stable disease within the first 24 weeks from randomisation, and dividing this by the total number of participants evaluable for response (according to RECIST Version 1.1) within the first 24 weeks.

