#### Secondary objectives (endpoints)

- Progression Free Survival
- Clinical benefit rate (SD + PR + CR) following 3 cycles (24 weeks) of treatment
- Time-to-treatment failure
- Safety/toxicity/tolerability
- Overall survival

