# ALT GIST

- For Arm B: C1 on the last day of imatinib administration C1 Wk7 (on the last day of regorafenib administration)
- For Arm B: C2 on the last day of imatinib administration and C2 Wk7 (on the last day of regorafenib administration)
- C4, and 8 Wk1 D1
- Upon relapse
- For the first 12 months, CT scans are performed 8 weekly from randomisation after which CT scans are performed 12 weekly until progression.
- A select group of Arm B patients will be enrolled in the PET substudy – Arm B patients will be further randomised to have PET scans either during the imatinib washout period, or during the regorafenib washout period. PET will be carried out on 2 occasions in each group and will be performed in Cycle 2 at the earliest, or in a subsequent cycle (at the first opportunity after a complete cycle of treatment without dose modifications is given).

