| Target Lesions                                            | Non-Target Lesions           | New Lesions | Overall Response* | Best Response for this category also requires                    |
|-----------------------------------------------------------|------------------------------|-------------|-------------------|------------------------------------------------------------------|
| Target lesions <math>\pm</math> non target lesions |                              |             |                   |                                                                  |
| CR                                                        | CR                           | No          | CR                | Normalisation of specified tumour markers, AND lymph nodes <10mm |
| CR                                                        | Non-CR/Non-PD                | No          | PR                |                                                                  |
| CR                                                        | Not all evaluated            | No          | PR                |                                                                  |
| PR                                                        | Non-PD/
not all evaluated | No          | PR                |                                                                  |
| SD                                                        | Non-PD/
not all evaluated | No          | SD                | Documented at least once $\geq 4$ wks. from baseline             |
| Not all evaluated                                         | Non-PD                       | No          | NE                |                                                                  |
| PD                                                        | Any                          | Any         | PD                |                                                                  |
| Any                                                       | PD                           | Any         | PD                |                                                                  |
| Any                                                       | Any                          | Yes         | PD                |                                                                  |

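### Section 9.3 labels the clinical benefit rate as a 24-week result but counts any response or stable disease within 24 weeks, so a patient stable at week 8 who progresses at week 16 counts as a success

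*Protocol*

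**What the plan says.** The secondary objectives, in the synopsis and again in section 3, list "Clinical benefit rate (SD + PR + CR) following 3 cycles (24 weeks) of treatment". The heading of section 9.3 likewise places the rate at three cycles (24 weeks).

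The body of 9.3 takes as numerator the participants assessed as "having a complete response, partial response or stable disease within the first 24 weeks from randomisation". It forms the rate by "dividing this by the total number of participants evaluable for response (according to RECIST Version 1.1) within the first 24 weeks".

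Three other places bear on how this rule works:

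- **Scan schedule (section 8.2.2):** "For the first 12 months, CT scans are performed 8 weekly from randomisation". Within the window, scans therefore fall at weeks 8, 16 and 24.
- **Appendix 2, Table 1:** for stable disease to stand as best response it must be "Documented at least once", at 4 weeks or more from baseline. The footnote on confirmation covers complete and partial response only.
- **Appendix 2, section 1:** a participant is evaluable after at least one cycle and a re-evaluation of disease. Objective progression before the end of cycle 1 also makes a participant evaluable.

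Section 13.2 states that the analyses include every randomised patient.

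**The concern.** The objective and the heading describe a status reached after 24 weeks. The body describes something that happens at some time during those weeks. These are different quantities, and no other section says which one governs.

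The trial is non-comparative, and section 13.1 calls its measured activity primarily descriptive. A descriptive rate has to mean what its label says. A reader of the report would take a 24-week clinical benefit rate to be the share of patients still controlled after three cycles. As worded, it mostly reports who had not progressed by the first scan. Arm B adds drug-free intervals and a second agent, so whether control lasts through cycles 2 and 3 is the informative part of this endpoint. The present wording leaves that part out.

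**Working it through.** The protocol states no target, threshold or power for this rate, so there is no figure to reproduce. The check is to apply the rule to one patient and then to illustrate the size of the difference.

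**1. One patient under both readings.** Take stable disease at week 8 and progression at week 16.

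- *Numerator, body of 9.3.* The week-8 scan lies inside the 24 weeks and shows stable disease, so the patient is counted. Week 8 is past the 4-week minimum in Appendix 2, and stable disease needs no confirmation, so the appendix does not prevent this. No rule withdraws the patient at week 16.
- *Denominator.* One 8-week cycle and a re-evaluation make the patient evaluable.
- *Result.* A success under the body of 9.3, and a failure under the objective and the heading.

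**2. Direction.** Any evaluable patient with disease control at week 24 also has a qualifying assessment within 24 weeks. The first group is contained in the second, so among evaluable patients the rate as written can equal the week-24 rate or exceed it, but cannot fall below it. This takes the week-24 scan as lying inside the window.

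**3. Illustration of size.** Inputs:

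- Median PFS of about two years, from section 1, for imatinib alone.
- 38 patients in the alternating arm and 22 in the control arm, from section 13.1.
- Assumed: exponential PFS; every patient evaluable; the rate as written approximated by S(8 weeks) and the rate as labelled by S(24 weeks).
- Assumed: medians of 18 and 30 months as a range.

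Formula: S(t) = exp(−ln 2 × t / m), with m the median in weeks. For 24 months, m = 24 × 365.25 / 12 / 7 = 104.4 weeks.

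- S(8) = exp(−0.6931 × 8 / 104.4) = 0.948
- S(24) = exp(−0.6931 × 24 / 104.4) = 0.853

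| Median PFS | S(8 weeks) | S(24 weeks) | Gap, points | Patients of 38 | Patients of 22 |
|---|---|---|---|---|---|
| 18 months (assumed) | 0.932 | 0.809 | 12.3 | 4.7 | 2.7 |
| 24 months (section 1) | 0.948 | 0.853 | 9.6 | 3.6 | 2.1 |
| 30 months (assumed) | 0.958 | 0.880 | 7.8 | 3.0 | 1.7 |

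Gaps are taken before rounding. At 24 months the alternating arm would show about 36 of 38 as written and about 32 of 38 at week 24.

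**4. Denominator.** Under Appendix 2, section 1, early objective progressors stay in as failures. Those who drop out leave or die before completing a cycle or being re-evaluated, without objective progression. Symptomatic deterioration without a scan belongs here too, because Appendix 2 says it is not objective progression. Leaving these patients out does not fit section 13.2, which includes all randomised patients.

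**The case against.** **The sentence can be read with its heading.** Section 9.3 mentions neither any scan nor best response, and section 9.1 determines status at each assessment. On that view 9.3 simply means status after three cycles, and bringing in the stable-disease row of Appendix 2 is an inference. It is fair that 9.3 does not invoke best response. The finding does not need it to: the appendix matters only because it sets no longer minimum for stable disease that would stop the week-8 scan from counting. The plain sense of the sentence remains a window, and nothing reconciles it with the objective.

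**The consequences are limited.** This stands. The endpoint is secondary, with no hypothesis or decision rule attached. The size comes from a constant-hazard model, and its median was observed on continuous imatinib, not on the alternating regimen.

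Three stronger readings are tempting, and the protocol does not support them:

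- A reader might infer that the evaluable denominator removes early progressors. Appendix 2 keeps them in.
- A reader might infer that the rate would be close to 100% for any active drug. Nothing in the protocol says so, and the illustration gives about 93% to 96%.
- A reader might infer that the trial cannot show loss of control between weeks 8 and 24. PFS (9.2) and time to treatment failure (9.4) both capture it, with 8-weekly scans and Kaplan-Meier description. They do not, however, correct a mislabelled benefit rate.

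**Conclusion.** The inconsistency is real and rests on the text alone: the body of 9.3 does not measure what its heading and the objective name. The direction is settled, since among evaluable patients the rate as written is never below the week-24 rate. The size is an illustration that depends on the exponential assumption and a borrowed median: about 95% against 85%, a gap of 9.6 points, or 12.3 to 7.8 points over medians of 18 to 30 months. In the alternating arm that is roughly 3 to 5 patients of 38. The evaluable denominator adds a smaller conflict with section 13.2, confined to patients lost before re-evaluation without objective progression. The 9-month response endpoint is untouched, and no stated decision turns on this rate. It should be corrected, but it does not threaten the main conclusion of the trial.

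**What to change.** Replace the definition in 9.3 with one that matches the objective: the proportion of patients with complete response, partial response or stable disease at the week-24 scan and no progression or death before it.

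- State the window for that scan. Section 8.1 allows 3 days either side of the due date, so a scan done slightly late would fall outside a strict 24-week limit.
- Use all randomised patients as the denominator, in line with section 13.2, and give the evaluable-set rate as a sensitivity analysis.
- Say openly that under this definition a patient with no week-24 assessment is not counted as having benefit.

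The cost is a short rewording of 9.3. It needs no new scans or visits, since the week-8, week-16 and week-24 scans are already scheduled. The downside is that the reported rate will be lower.
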